## Abstract

**Background:**

Colorectal cancer (CRC) is the third most common cancer worldwide, with a median age of 72–75 years at diagnosis. Curative treatment usually involves surgery; if left untreated, symptoms may require emergency surgery. Therefore, most patients will be accepted for surgery, despite of high age or comorbidity. It is known that elderly patients suffer higher risks after surgery than younger patients, in terms of complications and mortality. Assessing frailty and offering frail elderly patients individualized treatment according to the comprehensive geriatric assessment (CGA) and care concept has been shown to improve the outcome for frail elderly patients in other clinical contexts.

**Methods:**

This randomized controlled multicentre trial aims to investigate if CGA and care prior to curatively intended surgery for CRC in frail elderly patients will improve postoperative outcome. All patients ≥ 70 years with surgically curable CRC will be screened for frailty using the Clinical Frailty Scale (CFS-9). Frail patients will be offered inclusion. Randomization is stratified for colon or rectal cancer. Patients in the intervention group are, in addition to standard protocol, treated according to CGA and care. This consists of individualized assessments and interventions, established by a multiprofessional team. Patients in the control group are treated according to best known practice as stipulated by Swedish colorectal cancer treatment guidelines, within an enhanced recovery after surgery (ERAS) setting. The primary outcome is 90-day mortality. Secondary outcomes are the length of hospital stay and total number of hospital days within 3 months, discharge destination, 30-day readmission, ADL, safe medication assessment, CFS-9 score, complications, Health-Related Quality of Life (HRQoL) at 2-month follow-up in comparison to baseline measurements, health economical calculations including cost-effectiveness analysis based on costs of hospital care and primary care, mortality and HRQoL at baseline, 2- and 12-month follow-up and all-cause 1-year mortality.

**Discussion:**

The trial is the first of its size and extent to investigate intervention with CGA and care prior to surgery for CRC in frail elderly patients. If this addition proves to be favourable, it could have implications on future care of frail elderly patients with CRC.

**Trial registration:**

ClinicalTrials.gov NCT04358328. Registered on 4 February 2020

**Supplementary Information:**

The online version contains supplementary material available at 10.1186/s13063-022-06883-9.

## Administrative information

Note: the numbers in curly brackets in this protocol refer to SPIRIT checklist item numbers. The order of the items has been modified to group similar items (see http://www.equator-network.org/reporting-guidelines/spirit-2013-statement-defining-standard-protocol-items-for-clinical-trials/).

## Introduction

### Background and rationale {6a}

Colorectal cancer (CRC) is the third most common cancer form worldwide. Curative treatment involves surgical excision, in many cases in combination with chemo- and/or radiation therapy [1]. The incidence of CRC increases with higher age [1, 2]. In Sweden, the median age of diagnosis of colon cancer is 75 years and the highest number of new cases is in the age group 80–84 years. In terms of rectal cancer, the median age of diagnosis is 72 [3, 4]. As well as age being a risk factor for developing colorectal cancer, it is also known that mortality rates after treatment are higher in the elderly compared to younger CRC patients [5, 6]. Especially the postoperative morbidity and mortality in the first year after surgery are higher in the elderly [7, 8]. The population in Sweden, as in most of the western world, is getting older [9, 10]. This has resulted in elderly patients receiving curatively intended surgery in a larger extent than before [8].

The enhanced recovery after surgery (ERAS) protocol is a multimodal concept covering the pre-, peri-, and postoperative phases striving towards raising the quality of postoperative recovery. Compliance with the ERAS guidelines in colorectal surgery results in a shorter length of hospital stay and in fewer complications and readmissions post-surgery and has thus established its existence in modern colorectal cancer surgery [11].

Research has been conducted to identify elderly patients of increased risk for complications in relation to surgery [6, 12–15]. Chronological age is a blunt way of assessing an individual’s risk, since there is a great diversity in both physical and mental capacity in older people, making the elderly a heterogenous group. Sometimes the term biological age is used to emphasize this fact [16]. The term frailty is recognized as a clinical syndrome of reduced reserves and increased vulnerability and can be used as a marker of biological age [17, 18]. There is an association between frailty and other medical conditions, ageing and degree of disability, but frailty has been established as an independent risk factor for death, decreased ADL-function and hospitalization amongst others [19]. The assessment of frailty enables the identification of elderly individuals in particular risk of adverse health effects [20, 21]. Multiple studies have shown that elderly frail patients suffer a higher risk of severe postoperative complications and mortality compared to elderly non-frail patients after elective surgery for colon and rectal cancer [6, 13, 14, 22–24]. Frailty has even been described as the most important predictor of 90-day mortality post-colon cancer surgery in elderly patients [6] and it correlates to increased hospital and overall health care costs post-colorectal cancer surgery [25].

Two main models are frequently used to describe the frailty syndrome, i.e. the accumulation of deficits model [17] and the frailty phenotype model [18]. The accumulation of deficits model encompasses an assortment of accumulated symptoms, impairments, diseases and disabilities. Fried’s frailty phenotype uses criteria as unintentional weight loss, muscle weakness, physical slowness, poor endurance and low physical activity. There are several different instruments for frailty assessment. The Canadian Study of Health and Ageing (CSHA) Clinical Frailty Scale (CFS-9) is one of the most commonly used frailty instruments in clinical practice [17, 19], and it is validated and easily applied [21–23]. It is based on the accumulation of deficits model and includes assessments of comorbidity, function and cognition and generates a frailty score which describes the patient’s level of frailty [26, 27].

Having targeted the group of frail elderly as high-risk patients, there is a need to gain knowledge on how this group could be treated and further optimized prior to surgery to improve outcomes [8, 22, 28, 29]. Comprehensive geriatric assessment (CGA) and care is a multidimensional, interdisciplinary diagnostic and therapeutic concept. The CGA and care concept has been shown to improve outcomes in frail elderly patients in other clinical contexts [30–32], for example in terms of hip fractures and vascular surgery [33, 34]. A previously published report has investigated CGA and care prior to CRC surgery but in a small context and with short intervention time, without being able to prove any advantages [28]. There is a current discussion on how to ensure adequate treatment of the elderly colorectal cancer patient and a need of consensus on how to balance the risk of discrimination based on chronological age on the one hand and overtreating patients relative their degree of frailty on the other hand. Evidence of a potential benefit of an individualized geriatric treatment in this context has not yet been established. Therefore, there is a need of a randomized controlled trial to further evaluate the supposed advantages of adding CGA and care to standard protocol for the treatment of frail, elderly colorectal cancer patients.

### Objectives {7}

This manuscript is a detailed description of the study design and methodology of the randomized controlled trial “The CRC Frailty study”. The study aims to evaluate if the addition of CGA and care prior to colorectal surgery in the frail elderly could improve postoperative outcome, compared to frail elderly receiving standard care, both within an enhanced recovery after surgery (ERAS) setting.

The primary hypothesis of the RCT is that preoperative intervention with CGA and care, in addition to the conventional pre-, peri-, and postoperative care, will improve 90-day mortality rates after surgery for colon and rectal cancer. Based on previous studies and data from the Swedish Colorectal Cancer Registry (SCRCR) (adjusted for age and ASA classification) [12–14, 35], we know that this group of patients suffer higher mortality rates than younger, robust patients, thus making it highly interesting to investigate whether our intervention can improve this hard endpoint. The secondary hypothesis is that the intervention will improve outcome and recovery after surgery measured as complications, specified in the secondary endpoints stated below.

### Trial design {8}

The study is a prospective, randomized, multicentre superiority trial conducted at departments of surgery performing colorectal cancer surgery in an ERAS setting, in Sweden. Patients will be randomized into two parallel groups: control and intervention. The patients in the intervention group will be treated according to CGA and care preoperatively by geriatric, nursing, physiotherapist and dietician assessments followed by targeted and individualized interventions. The patients in the control group will be handled according to conventional preoperative assessments by anaesthesiologist and standard ERAS care. The groups will be stratified for colon or rectal cancer.

## Methods: participants, interventions and outcomes

### Study setting {9}

The trial is conducted at county and university hospitals in Sweden. A list of participating centres and study sites can be obtained from ClinicalTrials.gov, https://clinicaltrials.gov/ct2/show/NCT04358328. At present, two centres are participating (a county hospital, the Department of Surgery, Norra Älvsborg Hospital (NÄL), Trollhättan, and a tertiary university hospital, the Sahlgrenska University Hospital, Gothenburg) and recruitment of 1–3 further centres is on-going. Potentially available participating centres are departments performing rectal and/or colon cancer surgery according to the ERAS concept, in Region Västra Götaland, Sweden. All levels of hospitals are welcome as this will improve the external validity.

### Eligibility criteria {10}

Inclusion criteria:Potentially curable colorectal cancer (according to cTNM)Age ≥ 70Frailty (defined as CFS-9 score of 4–8 (v2.0))

Exclusion criteria:Palliative situationPatient unable to understand study informationUrgent/emergent surgeryTerminally ill patient (CFS-9 score of 9)Estimated life expectancy < 6 monthsUnwillingness to take part in the study

Participating study centres are performing colorectal cancer surgery and applying an ERAS protocol. Participating centres must also be able to supply a multiprofessional CGA and care team consisting of internal medicine physicians/geriatricians, physiotherapists or occupational therapists, dieticians and nurses.

### Who will take informed consent? {26a}

Written and verbal information regarding the study will be given by the surgeon during the patient’s first visit at the outpatient clinic. A study nurse will have a follow-up telephone call and ask regarding participation. If a patient chooses to participate, an informed consent will be filled out at the day of interventions and obtained from one of the surgeons at the clinic. Eligible patients declining participation will be registered in a log. Written patient information and informed consent documents, in English versions, are attached to this article as Additional files 1 and 2.

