#### Intervention group

The patients in the intervention group receive standard care according to the description above but with the CGA and care intervention in addition. As soon as a patient has been randomized to the intervention group, they are scheduled for an “intervention day”, which takes place on pre-decided dates (once every week). During this day, each patient has an individual meeting with an internal medicine physician with geriatric profiling, a study nurse, a physiotherapist or occupational therapist and a dietician. The team conducting the screenings receives introduction about the intervention and education regarding the CGA concept prior to entering the study, and they are also able to address the local expertise of CGA if questions arise during the evaluations. Each profession evaluates the patient clinically and according to the determined screening tools and issues an individual action plan based on these results (Fig. 1). The recommendations are individually prescribed and based on the health care professional’s evaluations based on the standardized screening, according to the CRF. The instruments used by each profession at different measurement points are stated below (Table 1).

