#### Control group

The patients in the control group are assessed using some of the instruments that are used for the intervention group. These measurements are conducted by the regular ward staff (in general a nurse working at the surgery ward/outpatient clinic) at admission to hospital prior to surgery and at the postoperative outpatient visit (Table 2). These extra measurements are the only differences between the control group and patients not included in the trial treated according to standard protocol.

**Table 2 Tab2:** Screening instruments used for the control group, at baseline, at post-op visit (approximately 2 months post-op) and at 12 months post-op

Health care professional	Outcome and instruments	Time of measurements
Ward nurse/nurse at the outpatient clinic	- **Frailty**—*CFS-9* - **HRQoL**—*EQ*-5D-5L - **Cognition**—*MiniMental State Examination (MMSE)* - **Medication safety**—*Safe Medication Assessment (SMA) and list of medications* -** Dependence**—*Activities of Daily Living (ADL-step)* - **Nutrition**—*Mini-Nutritional Assessment-Short Form (MNA-SF)*	**CFS-9** - Baseline - Post-op visit **EQ-5D-5L** - Baseline - Post-op visit - 12 months post-op **MMSE** - Baseline **SMA** and list of medications - Baseline - Post-op visit **ADL** - Baseline - Post-op visit **MNA-SF** - Baseline - Day of/day before surgery
Member of the project steering groups	- **Complications**—*Clavien-Dindo scale* - **Comorbidity**—*Charlson comorbidity index (CCI)*	**Complications** - Post-op visit **CCI** - Baseline - Post-op visit

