## Assignment of interventions: allocation

### Sequence generation {16a}

The allocation sequence is generated by the project leader manually in blocks of 10 (intervention/control). The envelopes are mixed, then numbered and drawn in numerical order as patients are included. The randomization is stratified for colon or rectal cancer.

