## Discussion

A majority of colorectal cancer patients are elderly, and in most cases, the treatment objective is to provide the same curative therapy as for younger patients. There have been significant improvements in the management of colorectal cancer in the elderly during recent years. Though, there is a growing interest in further optimizing the process, to decrease the higher mortality and complication rates, especially in the immediate postoperative phase. In other medical circumstances, an individualized plan and treatment according to CGA and care has improved outcomes for the group frail elderly. We know that frail elderly suffers higher risks of postoperative complications and mortality after colorectal cancer surgery and there is circumstantial evidence pointing in the direction of positive effects of CGA and care also for patients with colorectal cancer. However, there is no randomized intervention study of substantial size and quality to support this assumption.

Arguing for stretching the time span from diagnosis and treatment decision to surgery up to 8 weeks poses some ethical and practical concerns. Patients may be reluctant to participate in the study due to fear of progressive disease during the time until surgery. It may also be a larger psychological stress knowing that the cancer is left untreated for a longer time. However, our hypothesis is that the positive effect of the individualized CGA and care intervention on postoperative complications and mortality will outweigh the possible—but not scientifically shown—enhanced risk of progressive disease due to delayed treatment of the tumour. There is however no evidence in the literature that a delay of treatment of this timespan would have a negative effect on overall survival or disease-free survival [65–68]. There are rather indications that optimizing a patient’s medical situation preoperatively can improve outcomes after surgery, even if the time until surgery is somewhat extended. We have argued this in our application to the Ethics board and have gained approval from the Swedish Ethical Review Authority for this regimen. Also, the intervention team is in every case focused on keeping the intervention as short and effective as possible. As soon as the intervention does not provide further use or when the maximum time of 8 weeks is reached, the patient proceeds to surgery without further delay.

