The study is set up as a multicentre trial. There is a risk that routines differ between hospitals which could require deviations from the protocol. The CRFs and assessment tools are the same at every hospital which forces coherence to the most important variables of the study. Likewise, all participating hospitals are following the ERAS concept and the guidelines stipulated in the standardized care process of colorectal cancer published by the National Board of Health and Welfare in Sweden. This further strengthens the accordance between centres.

Another risk of conducting a randomized controlled trial is that the novel ideas and processes of the intervention could affect the way the health care professionals treat patients in the control group. Since the trial brings notice to the fact that frail elderly is a group at particular risk of adverse effects, it is possible that the staff at the clinic will treat participating patients in a different way, e.g. pay extra attention to symptoms suggesting postoperative complications or becoming more aware of perioperative nutrition problems etc. This could affect, and possibly, diminish the results from the study. To assure that the control group is treated according to standard clinical praxis, we have tried to separate the two groups as much as possible prior to surgery. The intention is to schedule the day of interventions, when the patients in the intervention group meet the CGA team, on a day where patients in the control group are not visiting the hospital. The health care professionals in the CGA team will not treat the control group during their stay at the hospital, in connection to their surgery.

We believe this trial could bring important light to the group of frail elderly in terms of surgery, primarily of colorectal cancer. It is clearly shown that this group is suffering poorer outcome after surgery, which also generates higher health care costs. If a CGA and individualized care treatment could decrease postoperative complication and mortality rates, as well as being cost-effective, it would be of great value in future care of frail elderly patients with colorectal cancer.

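### As written, consent is signed on a day that follows randomisation and exists only in the intervention arm, so refusal after allocation could occur in that arm alone

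*Protocol article*

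**What the plan says.** All references are to the protocol article.

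- **Who will take informed consent? {26a}.** The surgeon gives information at the first outpatient visit. Then: "A study nurse will have a follow-up telephone call and ask regarding participation". For those who agree, "an informed consent will be filled out at the day of interventions and obtained from one of the surgeons at the clinic". Eligible patients who decline are entered in a log. The text does not separate the two arms.
- **Intervention group.** "As soon as a patient has been randomized to the intervention group, they are scheduled for an" intervention day, held weekly on fixed dates.
- **Discussion.** To keep the groups apart before surgery, that day is meant to fall "on a day where patients in the control group are not visiting the hospital".
- **Control group.** Ward staff take the trial measurements at admission and again at the postoperative visit. No occasion for signing is named.
- **Sequence generation {16a} and Concealment mechanism {16b}.** Numbered opaque envelopes are drawn in order at the outpatient clinic as patients are included. Signed consent is not named as a condition for opening one.
- **Who will be blinded {17a}.** Neither patients nor caregivers are blinded.
- **Plans to promote participant retention {18b}.** Patients who choose to leave the trial are logged and nothing further is recorded. Those who deviate or miss follow-up are still checked against the mortality registry.
- **Statistical methods {20a} to {20c}.** Intention to treat is named, but the text does not say whether a randomised patient who refuses at signing belongs to the analysis set.

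**The concern.** If the form is signed on the intervention day, one arm is asked for its signature after learning the allocation, and the other has no stated time at all. Anyone who declines at that point has already been randomised. If such a patient is treated as never having joined, the exclusion comes after allocation and can happen only in the intervention arm.

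The primary endpoint is all-cause 90-day mortality. If those who refuse differ in risk from those who sign, removing them shifts mortality in one arm without any treatment effect. Naming intention to treat does not by itself prevent this. The retention section stops all recording for patients who choose to leave, so a refuser has no clear route to a recorded outcome.

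**Working it through.** **1. The order of events.** Setting the sections side by side gives:

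| Step | Intervention arm | Control arm |
|---|---|---|
| Information from surgeon | First outpatient visit | First outpatient visit |
| Telephone call about participation | Yes; order relative to envelope not stated | Yes; order relative to envelope not stated |
| Envelope opened | Outpatient clinic | Outpatient clinic |
| Intervention day | After randomisation | None |
| Written consent | On the intervention day | No time given |

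No section puts the signature before the envelope.

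**2. The article's own figure.** Sample size {14} gives 170 per group for 15% against 5%, with 80% power, alpha 0.05 and 5% loss. The two-sided pooled formula gives [1.960·√(2·0.10·0.90) + 0.842·√(0.15·0.85 + 0.05·0.95)]² / 0.10² = 140.1, so 141. With continuity correction this is 160, and 160/0.95 = 168.4, so 169, which agrees with 170 within rounding. The figure stands and does not change here.

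**3. Size of the possible bias.** Inputs from the article are 170 per group and 15% mortality. The other inputs are assumptions: no true effect, a share f of the intervention arm refuses after allocation and is left out, and refusers have mortality m.

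- Remaining intervention mortality = (0.15 − f·m)/(1 − f).
- Spurious difference = 0.15 − that value = f(m − 0.15)/(1 − f).

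For f = 10% (17 of 170) and m = 30%: (0.15 − 0.10·0.30)/0.90 = 0.133, a difference of 1.7 points.

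The false-positive rate uses a normal approximation for 170 against 170(1 − f) patients, with the pooled standard error for the critical value and the unpooled one for the distribution. For this case (170 against 153) the standard errors are 0.0389 and 0.0388. The rate is Φ((0.0167 − 1.96·0.0389)/0.0388) + Φ((−0.0167 − 1.96·0.0389)/0.0388) = 0.071.

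| f | m | Remaining arm | Spurious benefit (points) | Two-sided type I error |
|---|---|---|---|---|
| any | 15% | 15.0% | 0 | 5.0% |
| 5% | 30% | 14.2% | 0.8 | 5.5% |
| 10% | 30% | 13.3% | 1.7 | 7.1% |
| 10% | 40% | 12.2% | 2.8 | 11.1% |
| 20% | 30% | 11.25% | 3.75 | 15.6% |
| 20% | 40% | 8.75% | 6.25 | 37.8% |

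The sign can also reverse. With f = 10% and m = 5%, the remaining arm shows (0.15 − 0.005)/0.90 = 16.1%, which is 1.1 points against the intervention.

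**4. Power.** Without continuity correction, power is 0.87 with 170 per group, 0.85 with f = 10% and 0.82 with f = 20%. The issue is bias, not power.

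**5. Secondary: predictability of blocks.** The project leader makes the sequence by hand in blocks of 10. For 5:5 blocks, the best guess is right 5 + 2⁹/252 − 0.5 = 6.53 times in 10, and 10/6 = 1.67 allocations in 10 are certain in advance. Over the roughly 290 patients left (340 less about 50), that is about 48 allocations. These figures assume that someone knows the block boundaries and follows every allocation within a stratum.

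**The case against.** The strongest reply is that willingness is settled before allocation and the form only documents it. The nurse asks about participation by telephone, unwillingness is an exclusion criterion, and envelopes are drawn as patients are included. On this reading the logged decliners are people who said no when asked, not randomised refusers. That is a fair reading and may well be the practice. It does not remove the point, because the call is not placed before the envelope and oral agreement does not prevent refusal when the form is presented.

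It can also be said that intention to treat is stated repeatedly, and that mortality is cross-checked against the population registry for all participants. That limits the harm if everyone randomised counts as a participant. It does not clearly cover someone who refuses at signing, since the retention section stops recording for those who choose to leave.

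Three stronger readings are tempting, and the article does not support them:

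- A reader might infer that the arms are already not comparable. The article gives neither refusals after allocation nor the prognosis of refusers.
- A reader might take the Discussion's remark, "Patients may be reluctant to participate in the study due to fear of progressive disease during the time until surgery", as evidence of refusal in one arm. It concerns reluctance to join the study, which can act before allocation and on both arms alike.
- A reader might infer that controls never consent. The article only fails to give a time, and the full protocol and consent documents are not shown.

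Block predictability is a separate matter. The envelopes are opaque and numbered, and the surgeon enrols while a study nurse or local investigator assigns.

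**Conclusion.** The point holds as a conflict in the stated sequence and a risk to the primary comparison. The consent section ties the signature to a day that, by the intervention section and the Discussion, comes after randomisation and belongs to one arm. The bias that could follow is of unknown size and direction. It is zero if refusal is unrelated to risk or if everyone randomised is followed for death and analysed. Under the assumption of 10% refusing with 30% mortality, it is 1.7 points, small beside the 10-point target effect, with type I error near 7%. Only heavier assumptions, such as 20% refusing with 40% mortality, give a large distortion. All these refusal figures are assumed. If practice already puts the signature before the envelope, what remains is a wording error in the consent section. The hand-made blocks of 10 are a weaker, secondary issue and not part of this conflict.

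**What to change.** Reconcile the consent section with the intervention section, and state that:

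1. Written consent is obtained in both arms, at an existing outpatient contact before randomisation, and the envelope is opened only after signature.
2. Every randomised patient stays in the intention-to-treat set, with 90-day vital status taken from the population registry as far as consent allows.
3. Any refusals after allocation, including those among the approximately 50 patients already enrolled, are reported by arm.

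The cost is an amendment to the order of existing steps, with no change to 170 per group. The sponsor must identify which existing contact falls between the telephone call and the envelope, because the article does not name one. If there is none, the order of the call, the signature and randomisation has to be rearranged.

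Optional, for the remaining patients: replace the manual fixed blocks of 10 with a computer-generated list in varying block sizes, keeping the colon/rectum strata, prepared by someone who neither enrols nor assigns. The cost is one new list and a new set of envelopes.
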